# Metacognitive therapy versus exposure and response prevention for obsessive-compulsive disorder: study protocol for a randomized controlled trial

**DOI:** 10.1186/s13063-019-3381-9

**Published:** 2019-05-20

**Keywords:** Obsessive-compulsive disorder, Metacognitive therapy, Exposure and response prevention, Randomized controlled trial

## Abstract

**Background:**

The recommended psychological treatment of choice for obsessive-compulsive disorder (OCD) is exposure with response prevention (ERP). However, recovery rates are relatively modest, so better treatments are needed. This superiority study aims to explore the relative efficacy of metacognitive therapy (MCT), a new form of cognitive therapy based on the metacognitive model of OCD.

**Design and method:**

In a randomized controlled trial, we will compare MCT with ERP. One hundred patients diagnosed with OCD will be recruited in an outpatient mental health center in Rotterdam (the Netherlands). The primary outcome measure is OCD severity, measured by the Yale-Brown Obsessive Compulsive Scale (Y-BOCS). Data are assessed at baseline, after treatment, and at 6 and 30 months follow-up.

**Discussion:**

By comparing MCT with ERP we hope to provide an indication whether MCT is efficacious in the treatment of OCD and, if so, whether it has the potential to be more efficacious than the current “gold standard” psychological treatment for OCD, ERP.

**Trial registration:**

Dutch Trial Register, NTR4855. Registered on 21 October 2014.

**Electronic supplementary material:**

The online version of this article (10.1186/s13063-019-3381-9) contains supplementary material, which is available to authorized users.

## Background

### Phenomenology and treatment

Obsessive-compulsive disorder (OCD) is a severe mental condition which is characterized by intrusive thoughts (obsessions) and repetitive behaviors (compulsions) intended to neutralize anxiety induced by these thoughts [1]. OCD has been ranked among the 10 most debilitating disorders by the World Health Organization (WHO) and tends to be chronic without adequate treatment [48]. Both studies into pharmacological treatment, primarily with selective serotonin reuptake inhibitors (SSRIs), and studies into specific forms of psychological treatment supported the effectiveness of these treatment modalities in reducing symptoms of OCD [3]. The first-choice psychological treatment for OCD is exposure and response prevention (ERP) [31, 34, 37], a specific type of cognitive behavioral therapy (CBT) based on learning theory, which suggests that classical conditioning is responsible for the development of obsessions, whereas operant conditioning processes maintain anxiety and compulsive behaviors [27]. In ERP treatment, patients are exposed to anxiety-provoking stimuli (situations, objects, thoughts) combined with the strict prevention of performing ritual behaviors [26]. Since its introduction in 1966, the prognosis for OCD improved substantially. However, OCD remains a difficult disorder to treat. Although numerous studies have found statistically significant change and large improvements in OCD symptoms after ERP, the outcomes are sub-optimal for the majority of patients. More specifically: although about 60% of treatment completers achieve recovery, only approximately 25% of patients are asymptomatic following treatment [11, 14], which means that the majority of patients treated with ERP continue to experience distressing OCD symptoms. Furthermore, the overall effectiveness of ERP for OCD is attenuated by some limitations of the approach. As approximately 30% of patients with OCD refuse ERP or drop out from treatment prematurely, it is assumed that overall recovery rates are lower [30]. Moreover, these figures suggest that ERP might be hard to tolerate and is burdensome, which is supported by the finding that an important reason for not attempting ERP are the requirements of treatment (e.g. exposure to anxiety provoking stimuli [46]). So, although it can be concluded that ERP is efficacious, there is clearly room for improvement in the psychological treatment of OCD. It is assumed that this improvement could result from a better understanding in the mechanisms involved in the maintenance of the disorder.

### The metacognitive model of OCD

A recently developed theoretical account explaining the maintenance of OCD symptoms is the metacognitive model by Adrian Wells [42, 43]. In this model of OCD, two belief domains are assumed to be fundamental in the maintenance of the disorder. First, it is proposed that obsessions are misinterpreted because of metacognitive beliefs about the dangerousness, significance, and consequences of intrusive thoughts and feelings, the so-called fusion beliefs. Three classes of fusion beliefs are highlighted: thought action fusion (TAF); thought event fusion (TEF); and thought object fusion (TOF). TAF [32] refers to the belief that obsessional thoughts can lead to the commission of an action (e.g. “thinking about killing someone will make me do it”). TEF [42] refers to the belief that obsessional thoughts can make events happen (e.g. “thinking about a car accident means I will be involved in such an accident”) or mean an event has already occurred (e.g. “If I think I ran into someone with my car, I probably did it”). Finally, TOF [43] refers to the belief that thoughts or negative feelings can be passed into objects (e.g. “my feeling of evil could be passed into objects and from these objects to other people”). Once the fusion beliefs are activated, they give significance to obsessional thoughts and lead to appraisal of, and worrying about, the thoughts and consequently to feelings of anxiety and perceived threat. This anxiety primes a second domain of metacognitive beliefs: beliefs about the necessity of performing rituals in response to obsessive thoughts in order to reduce the perceived threat (e.g. “Counting to seven will restrain me from acting on my thoughts”). Consequently, patients with OCD engage in both overt and covert ritual behaviors and, thereby, use specific internal rules (instead of external observation) and so-called “stop signals” to determine how the ritual must be conducted and when it can be terminated. Such stop signals are often metacognitive experiences, such as a feeling of satisfaction (e.g. “I must wash my hands until ‘it feels right’”). They also use other neutralizing coping strategies such as monitoring for further intrusive experiences, which is seen as a counterproductive strategy as it increases the awareness and frequency of intrusive thoughts. The metacognitive model of OCD is illustrated in Fig. 1.

**Fig. 1 Fig1:**
[figure not shown]
Metacognitive model for OCD [42]

### Metacognitive treatment for OCD

Based on the metacognitive model, treatment should focus exclusively on modifying patients’ beliefs about the importance and power of intrusive thoughts and the necessity of performing rituals, instead of challenging the actual content of the obsessions and compulsions [12]. Although metacognitive therapy (MCT) uses comparable techniques as cognitive therapy (CT) for this purpose, such as verbal reattribution and behavioral experiments, the two approaches are fundamentally different [13]. For example, patients with OCD can describe appraisals in the domain of inflated responsibility, perfectionism, and intolerance of uncertainty. The metacognitive model proposes that such appraisals result from the activation of metacognitive beliefs about obsessions; consequently, it is not necessary to modify these lower order beliefs as is done in CT (e.g. by using the pie chart technique to compare the patient’s original estimated probability with a more realistic estimate of probability) [5, 17]. Targeting such lower order beliefs and automatic thoughts is seen as counterproductive as it just promotes further conceptual processing, such as worrying and rumination [15]. Instead, it is thought that modification of the metacognitive beliefs about the meaning and power of obsessions removes the need for further conceptual processing. Therefore, interventions are explicitly aimed at the metacognitive processes which perpetuate the continued maladaptive processing instead of attempting to modify the content of perseverative thinking (i.e. appraisals) [13].

So far, there is preliminary evidence supporting the efficacy of MCT for OCD. The clinical significance of treatment effects in the following mentioned studies is calculated using the standard criteria developed by Fisher and Wells [11, 14], based on the method of Jacobson and Truax [21]. Based on these criteria, patients are classified as recovered if they achieved a reduction of minimal 10 points on the Yale-Brown Obsessive Compulsive Scale (Y-BOCS [19]; a semi-structured interview for OCS) and a post-treatment score < 14. When achieving a post-treatment score < 7, patients are classified as asymptomatic. Using single case methodology, Fisher and Wells [12] found clinically significant improvements for four OCD patients with different clinical presentations who were treated individually with MCT. Two of the four participants were asymptomatic at both post-treatment and three-monthfollow-up assessments. Furthermore, Rees and Van Koesveld [33] found that seven out of eight participants in an open trial of group MCT for OCD reached criteria for a recovery status on the Y-BOCS at three-monthfollow-up (87.5%). In an additional study, Fitt and Rees [16] found similar clinically significant reductions among three patients treated with MCT using videoconference. In an open trial of individual metacognitive therapy among 25 patients with OCD, Van der Heiden et al. [39] found statistically significant reductions on all outcome variables. Moreover, in terms of clinically significant results, 74% of the treatment completers (*n* = 19) were classified as recovered after treatment and 47% as asymptomatic. At follow-up, this increased to 80% and 67% respectively. Finally, Simons et al. [35] found positive outcomes of MCT in comparison to ERP in the treatment of pediatric OCD in a case series design. Together, these findings suggest that MCT might be an efficacious treatment for OCD and deserves controlled evaluation. The present trial has been initiated to compare the relative efficacy of MCT with ERP, in an outpatient clinical sample of patients with OCD. Our main hypothesis is that MCT is more efficacious than ERP in the treatment of OCD in terms of both statistically and clinically significant improvements, both directly after treatment (primary outcome) and at follow-up.

## Design and methods

### Design

We will conduct a randomized controlled trial (RCT) with a pretest–post-test (primary outcome) 6-month–30-month follow-up-design. Patients will be recruited from consecutive referrals to the Anxiety Disorders department of PsyQ, an outpatient community mental health center in the Netherlands. After screening for eligibility and informed consent, we will randomize the patients into two groups: MCT and ERP. The number of excluded patients and refusers and their reasons are registered. Participating patients will be assessed by self-report measures and semi-structured clinical interviews administered by a research assistant who is blind to group allocation at entry (pre-treatment), after the last treatment session (post-treatment – primary outcome), six months (first follow-up) after treatment completion and 30 months (second follow-up) after treatment has ended. The latter assessment is included to answer a secondary research questions on the durability of both the ERP and MCT effect on the long term. Due to a lack of studies with follow-up periods of > 1 year [9, 47], the information on longer-term effects are unknown. In case of drop-out, measurements and interviews are also administered directly after treatment had ended whenever this is possible. The study has received ethical approval from the Medical Ethical Committee of the Leiden University Medical Centre (LUMC) (protocol number NL50201.058.14) and is registered in the Dutch Trial Register (protocol number NTR4855). All data will be stored anonymously; there is a data safety and monitoring board for the study. Figure 2 shows a flowchart of the study from patient enrollment up to data analysis and reporting. This study follows the “guidance of standard protocol items: recommendations of interventional study’s (SPIRIT).” The SPIRIT figure template is displayed in Fig. 3. In addition, the SPIRIT checklist can be found in Additional file 1.

**Fig. 2 Fig2:**
[figure not shown]
*Flowchart* of the study

**Fig. 3 Fig3:**
[figure not shown]
Standard protocol Items: Recommendations for Interventional Trials (SPIRIT). Diagram of enrolment, interventions and assessments over time. MCT metacognitive therapy, ERP exposure and response prevention, SCID-I Structured Clinical Interview for DSM Axis I Disorders. Primary outcome measure: Yale-Brown Obsessive Compulsive Scale (Y-BOCS). *Secondary outcomes: Padua Inventory-Revised (Padua IR); The Symptom Checklist (SCL-90); The Beck Depression Inventory, 2nd version (BDI-II); World Health Organization Quality of Life (WHOQOL-Bref); Obsessive Belief Questionnaire (OBQ-44). **Process measures: Thought Fusion Instrument (TFI); and Beliefs About Rituals Inventory (BARI)

### Sample size

There are no studies available directly comparing ERP with MCT. We chose to design our study with enough statistical power to enable us to detect a medium between-group effect (Cohen’s *d* = 0.5 [6]) from baseline to post-treatment. We chose for this medium between-group effect because expecting a larger difference between the two treatment groups does seem unrealistic since numerous studies have found statistically significant change and large improvements in OCD symptoms after ERP. On the other hand, designing our study to enable us to detect a small between-group effect is of less relevance for clinical practice. We used the statistical method presented by Liu and Liang [22] for sample size calculations for studies with correlated observations. To achieve a power of 0.80 with four measurement points with a correlation of 0.5 between repeated measures (standard value) and to detect a medium effect size (Cohen’s *d* = 0.50) between the two treatment conditions over time on the primary outcome measure, severity of OCD symptoms, and an expected drop-out rate of 20%, the minimal sample size necessary in each condition is 50.

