#### Primary outcome

The primary outcome of interest for this MCT superiority study is OCD severity at post-treatment, which will be measured with the Y-BOCS [19], a semi-structured interview and the “gold standard” for measuring OCD symptoms. The Y-BOCS is a clinician-ratedsemi-structured interview designed to rate the severity of both obsessions and compulsion. The Y-BOCS consists of 10 items rated 0–4 (range = 0–40). The Y-BOCS has been shown to have good psychometric properties and is sensitive for measuring treatment effects [40]. Further, good internal consistency for both the subscales (obsessions and compulsions) and for the total score of the Y-BOCS has been reported [18].

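### The 50 per arm comes from a four-visit average that counts baseline; for the declared post-treatment endpoint, power at d = 0.5 is about 0.72, not 0.80

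*Protocol article*

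**What the plan says.** The Sample size section sets the target as a medium between-group effect, d = 0.5, "from baseline to post-treatment". The calculation that follows uses a method for correlated observations and is worded differently: "To achieve a power of 0.80 with four measurement points with a correlation of 0.5 between repeated measures (standard value", for an effect "between the two treatment conditions over time on the primary outcome measure, severity of OCD symptoms". With 20% drop-out it arrives at 50 per condition.

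The Abstract gives the schedule: "Data are assessed at baseline, after treatment, and at 6 and 30 months follow-up". That is four assessments in all, so the four measurement points must include baseline.

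The Primary outcome section is explicit: "The primary outcome of interest for this MCT superiority study is OCD severity at post-treatment". The Design section and the main hypothesis at the end of the Background also mark the post-treatment assessment as primary.

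The Statistical analysis section adjusts the mixed models for baseline, tests two-sided at 0.05, and calls the completer sample (at least eight sessions, no medication change during treatment) the primary analysis. No power is given for the post-treatment comparison on its own.

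**The concern.** The section names one target, the effect at post-treatment, and computes the sample size for another, a difference averaged over four visits. Averaging correlated measurements reduces variance, so fewer patients are needed than for one visit. The formula also credits every visit with the full d = 0.5, including baseline, where randomisation makes the expected difference zero.

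The stake is how the trial's result is read. The protocol regards differences larger than medium as unrealistic, so power at d = 0.5 is the figure that matters. If the trial is described as having 0.80 power for its primary comparison and has less, a null result would be taken as stronger evidence against a medium advantage of MCT than it is.

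**Working it through.** **Inputs.** From Sample size: power 0.80, m = 4, correlation ρ = 0.5, d = 0.5, 20% drop-out, 50 per arm. From Statistical analysis: two-sided 0.05 (the Sample size section does not state alpha), baseline adjustment, completers as the primary analysis. Allocation is equal.

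**Step 1: reproduce the plan's figure.** For a time-averaged difference with equal correlations,

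n per arm = 2(z₀.₉₇₅ + z₀.₈₀)² [1 + (m − 1)ρ] / (m d²).

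With m = 4: 2 × (1.960 + 0.842)² × 2.5 / (4 × 0.25) = 39.2, so 40. Then 40/0.8 = 50, an exact match.

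Other values of m with the same test and drop-out do not give 50:

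| m | n before rounding | n analysed per arm | n randomised per arm |
|---|---|---|---|
| 1 | 62.8 | 63 | 79 |
| 2 | 47.1 | 48 | 60 |
| 3 | 41.9 | 42 | 53 |
| 4 | 39.2 | 40 | 50 |

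**Step 2: power for the declared endpoint.** Baseline adjustment at one post-treatment visit leaves a residual variance of 1 − ρ² = 0.75 in SD² units. With 40 analysed per arm:

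- standard error = √(0.75 × 2/40) = 0.194
- noncentrality = 0.5/0.194 = 2.58
- degrees of freedom = 80 − 3 = 77
- power (noncentral t) = 0.72; the normal approximation gives 0.73.

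Solving the same expression for 0.80 power gives a detectable effect of d = 0.55.

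**Step 3: dependence on the assumptions** (d = 0.5, baseline-adjusted, noncentral t).

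| Correlation, 40 per arm | Power |
|---|---|
| 0.4 | 0.67 |
| 0.5 | 0.72 |
| 0.6 | 0.79 |
| 0.7 | 0.87 |

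| Analysed per arm, correlation 0.5 | Power |
|---|---|
| 38 | 0.70 |
| 40 | 0.72 |
| 45 | 0.77 |
| 50 | 0.82 |

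At the protocol's correlation, 0.80 is thus reached only if almost nobody is lost. At its drop-out rate, it is reached only if the correlation is somewhat above 0.6.

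**The case against.** Several points on the other side have weight.

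- **The correlation is a convention.** The protocol uses "a correlation of 0.5 between repeated measures (standard value", which is not an estimate from data. A higher baseline-to-post correlation would restore the power. This stands, and it is why the range should be shown. It does not support the stated 0.80, which was not obtained that way.
- **The number analysed may exceed 40.** The Design section plans post-treatment assessment of drop-outs where possible, and an intent-to-treat analysis uses all available data. This also stands as a sensitivity. But completers are named as the primary analysis and the plan itself allows for 20% loss, so 40 is the plan's own figure. A mixed model might also recover a little information from later visits; that was not computed.
- **An averaged effect is not underpowered.** For a constant d = 0.5 over the three post-baseline visits, baseline-adjusted and with 40 complete patients per arm, the variance is 2/3 − 0.25 = 0.417 and power is about 0.93 (normal approximation). That is correct, but it is not the declared primary endpoint.

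A reader might also infer more than the documents support:

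- **That power is only 0.60.** This is the figure for an unadjusted post-treatment comparison with 40 per arm. The protocol fixes baseline adjustment, so it does not describe the planned analysis.
- **That 20% drop-out contradicts the protocol's own figures.** The Background says "As approximately 30% of patients with OCD refuse ERP or drop out from treatment prematurely", which mixes refusers with drop-outs; patients who decline at entry do not reduce the randomised sample. The pilot, "In an open trial of individual metacognitive therapy among 25 patients with OCD", had 19 completers, so 6 of 25 (24%) were lost. The exact 95% interval is about 9% to 45%, which is too wide to contradict 20%.
- **That power is 0.56.** A zero difference at baseline and 0.5 at the other three visits average to 0.375, and the four-visit formula then gives 0.56. This shows that the formula is unsuitable, but no planned test compares that average.

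**Conclusion.** The point holds. The stated power of 0.80 belongs to a four-visit average including baseline and does not describe the primary comparison. On the protocol's own inputs (d = 0.5, correlation 0.5, two-sided 0.05, baseline adjustment, 40 analysed per arm) power at post-treatment is about 0.72. The chance of missing a true medium effect is then about 28% rather than 20%.

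This is a moderate shortfall. It rests on the correlation of 0.5 and on 40 being analysed, and either could turn out more or less favourable. It does not show that the trial is too small to be useful or that recruitment must rise. What is wrong is the figure attached to the primary endpoint and the calculation offered for it.

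**What to change.** Keep N = 100. In the Sample size section, replace the four-measurement justification with a calculation for the baseline-adjusted Y-BOCS difference at post-treatment. State that 50 randomised per arm, 20% loss and a baseline-to-post correlation of 0.5 give about 0.72 power for d = 0.5, and that d = 0.55 is detectable with 0.80 power. State the two-sided 0.05 level there as well. Add the two short sensitivity tables above, for the correlation and for the number analysed per arm, and say that 40 assumes the completer analysis with 20% loss.

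The cost is one rewritten paragraph and a slightly less favourable stated power. No extra patients or procedures are needed, so the change is feasible with 68 participants already randomised at publication.

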### Participant enrollment and randomization

One hundred adult patients (aged 18–65 years) with a primary diagnosis of OCD will be recruited from consecutive referrals to the Anxiety Disorders department of PsyQ, an outpatient community mental health center in the Netherlands. Diagnosis of OCD will be established using the SCID-I [10], a diagnostic interview based on the DSM-IV, because diagnostic instruments based on the DSM-5 [1] were not yet available at the development phase of this study. To enhance the clinical representativeness of the sample, exclusion criteria are kept to a minimum. Patients are only excluded if they currently: (1) meet DSM-IV-TR criteria for severe major depressive disorder or substance use disorder (other than smoking) that requires immediate treatment, psychotic disorder, or bipolar disorder; (2) have mental impairment or an organic brain disorder; or (3) had a change in medication type or dose in the six weeks before assessment or during treatment (see Fig. 2). The presence of other co-morbid diagnosis or previous treatment for OCD are not exclusion criteria. Potential participants will receive extensive information about the design and procedures of the study at the end of the clinical screening. Following informed consent, patients will be randomly assigned to the MCT or ERP condition. Randomization will be done by using www.randomization.com, an online generator which randomizes each individual to a treatment condition by using the method of randomly permuted blocks [24]. With randomly permuted blocks, participants are assigned to a treatment condition in blocks to ensure that equal numbers of individuals have been assigned to each treatment, not only at the end of the study but also at various intermediate time points. The generator also randomizes the block sizes (range = 1–4 per group), to ensure that it is unknown when a block is finished; it is not possible to guess the remaining treatment allocation. The process of allocation of cases to intervention conditions will be done by an independent employee of the participating mental health care center using the generated randomization plan. Patients will be allocated to treatment conditions in order of entry. The investigators and therapists have no insight in the randomization plan.

To control for therapist effects, all therapists will deliver both treatments in blocks but not in parallel. For this reason, in the first two years of the study, half of the therapists from each site deliver MCT while the other half does ERP. Two years later, treatment conditions will be crossed over.

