Fixed effects in our model will be time, treatment, and their interaction. In case of missingness, we will add these variable(s) also as fixed effects. The Benjamini–Hochberg procedure is applied to the significances of the time*treatment interaction *p*-values (two-sided *p* < 0.05) of the different outcome measures. The time variable will be treated categorically, with the first post-baseline measurement as the reference category. To accommodate the modeling of correlation among repeated measurements, we impose a first order autoregressive (AR (1)) structure on the residuals. Next, the interaction effect between time and group will be explored by analyzing the estimated marginal means at different time points. We expect a significant interaction effect between time and group, which means that scores change differently over time in the two treatment conditions. More specifically, we expect a more negative time trend for MCT than for ERP, indicating that the measurement scores in the MCT condition decline more over time than in the ERP condition. To gain further insight into the statistical significance of the improvements achieved in the two treatment conditions, we will perform a least significant difference test with the estimated marginal means to compare changes between treatment conditions. In accordance with the linear mixed models, we expect a statistically significant decline in both treatment conditions between pretest and post-test, but no statistical differences between post-test and both follow-up measures. To allow for comparison with other studies into the effectiveness of ERP and MCT for OCD, Cohen’s *d* statistic ((mean 1 – mean 2) / pooled SD) will be employed to calculate within-group effect sizes (ES) for changes on outcome measures and to evaluate between-group differences. We will calculate Cohen’s *d* statistics for both intent-to-treat samples by using multilevel analysis with all available data and completer samples (our primary analysis: minimum of eight treatment sessions and no change in medication during treatment will be managed as criteria for each patient to can be classified as treatment completer). Based on previous research, we expect a large within-treatment ES for both treatment conditions (Cohen’s *d* > 0.8). We expect a medium between-group ES in favor of MCT. In addition, the clinical significance of treatment effects and amount of drop-out will be examined also to gain further insight into the clinical value of the two treatment conditions.

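### Exclusion criterion 3 includes a medication change during treatment, which is known only after randomisation, and it conflicts with the protocol's own analysis-set definitions

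*Protocol article*

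**What the plan says.** Three places in the protocol article deal with this.

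- **Participant enrollment and randomization.** The list of exclusions opens with "Patients are only excluded if they currently". Its third item covers patients who "had a change in medication type or dose in the six weeks before assessment or during treatment", and the sentence refers to Fig. 2.
- **Statistical analysis, Outcomes.** Effect sizes are to be calculated for "intent-to-treat samples by using multilevel analysis with all available data and completer samples". The completer analysis is labelled primary, and its conditions are a "minimum of eight treatment sessions and no change in medication during treatment will be managed as criteria for each patient". No medication condition is attached to the intent-to-treat sample.
- **Interventions.** A completer is defined by at least eight sessions. Medication is not mentioned.

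The order of events is clear. The Design section says "After screening for eligibility and informed consent, we will randomize the patients into two groups: MCT and ERP", and the enrolment section says "Following informed consent, patients will be randomly assigned to the MCT or ERP condition".

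**The concern.** Criterion 3 joins a baseline condition (a change in the six-week window before assessment) to an event in the patient's course after allocation. The second part cannot be checked at screening. As an exclusion, it can act only by removing people who have already been randomised.

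Such removal is unlikely to be neutral. A patient who responds poorly or finds therapy hard to bear may be more likely to have medication altered. The Background suggests that ERP can be hard to tolerate, and the Discussion suggests that MCT may be less burdensome. The protocol itself therefore gives a reason why changes could differ between the arms. Conditioning on such an event would compromise the randomised comparison of post-treatment Y-BOCS.

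Making the intent-to-treat analysis primary would not settle the matter by itself. An analysis of all available data covers only what was collected. The Design section provides for assessing drop-outs after treatment where possible, but the article does not say what happens to a randomised patient who meets the second half of criterion 3.

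**Working it through.** **Step 1. The passages side by side.**

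| Section | Role of a medication change during treatment |
|---|---|
| Participant enrollment and randomization | Exclusion criterion |
| Statistical analysis, Outcomes | Disqualifies from the completer set; no condition on the intent-to-treat set |
| Interventions | Absent from the completer definition |

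These cannot all be followed. If the enrolment section is applied literally after randomisation, changers leave the trial and the intent-to-treat set is selected. If the Outcomes section governs, they stay in the intent-to-treat set and leave only the completer set. If the Interventions definition governs, they stay in both.

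**Step 2. The plan's own sample size.** Inputs from the Sample size section: d = 0.50, power 0.80, m = 4 measurements, correlation 0.5, drop-out 20%. Two-sided alpha of 0.05 is taken from the Outcomes section, because the Sample size section states none.

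- Variance factor: [1 + (m − 1)ρ]/m = (1 + 3 × 0.5)/4 = 0.625.
- n per arm = 2(1.960 + 0.842)²/0.5² × 0.625 = 39.24, rounded up to 40.
- With drop-out: 40/0.8 = 50, which matches the stated figure.

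The only stated allowance is for drop-out. None is stated for medication changers.

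**Step 3. Illustrative shift in an arm mean.** The protocol gives no rate of medication change, so these inputs are assumptions. If a share p of an arm is removed and those patients lie δ SD from their arm mean, the mean of those kept moves by pδ/(1 − p).

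| p | δ = 0.5 | δ = 1 |
|---|---|---|
| 0.05 | 0.025/0.95 = 0.026 | 0.05/0.95 = 0.053 |
| 0.10 | 0.05/0.90 = 0.056 | 0.10/0.90 = 0.111 |
| 0.15 | 0.075/0.85 = 0.088 | 0.15/0.85 = 0.176 |

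The top value is 0.176/0.5 = 0.35 of the target effect. It requires 15% removed from one arm, none from the other, and changers a full SD worse. If both arms lose patients, the bias is the difference between the two shifts. At δ = 1 with 5% against 15%, that is 0.176 − 0.053 = 0.12 SD. With equal p and δ in both arms it is zero.

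**Step 4. Illustrative power.** Power = Φ(0.5/√(2 × 0.625/n) − 1.96), with 5–15% of the 40 evaluable per arm also removed and no overlap with drop-out.

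| Further removal | n per arm | Power |
|---|---|---|
| 0% | 40 | 0.807 |
| 5% | 38 | 0.787 |
| 10% | 36 | 0.765 |
| 15% | 34 | 0.741 |

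**The case against.** A reader might infer that even the intent-to-treat set is selected, and that the plan leaves no unselected estimate. The document does not say so, and its Outcomes section points the other way. Absence of a medication change is attached there only to completers, in contrast to an intent-to-treat sample using all available data. That condition would be redundant if changers had already left the trial. The exclusion list also opens in the present tense, as a description of status at screening. Nothing states that a randomised patient is withdrawn, left unassessed or dropped from analysis. Fig. 2, to which the criterion refers, is not shown and might clarify where the rule applies.

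This objection stands against the unconditional claim: selection of the intent-to-treat set follows only from a literal application of criterion 3 after randomisation. It does not rescue the criterion. A change during treatment cannot be a status at screening, and staff who follow the enrolment section could remove patients whom the Outcomes section expects to analyse.

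Two cautions about size also stand. Poor response and poor tolerance could lead to both drop-out and medication change, so the two losses probably overlap and the power figures lean pessimistic. The direction of bias is not certain either: a change in medication could improve the post-treatment score, in which case changers would not be the worse patients.

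**Conclusion.** The point holds as a defect in the criterion and an unresolved conflict between sections. A post-randomisation event is listed as an exclusion. The same event is used elsewhere only to define completers, and a third section omits it. The completer set, which the plan labels primary, is selected on this event under the Outcomes definition. Whether the intent-to-treat set is also selected depends on which section governs, and the text does not settle that.

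The size is unknown, because no rate of medication change is given. The range of 0.03–0.18 SD assumes removal of 5–15% from one arm only and changers 0.5–1 SD worse than their arm mean. It shrinks as removal becomes similar in the two arms, and its sign depends on how changers fare. The fall in power from 0.81 to between 0.79 and 0.74 assumes removal in both arms with no overlap with the 20% drop-out. The case for amendment rests on the contradiction, and does not need the top of either range.

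**What to change.** Reconcile the three sections.

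1. End exclusion criterion 3 at the six-week window before assessment, so that it contains only what can be known before randomisation.
2. State that randomised patients whose medication later changes continue to be assessed at all planned points and are analysed in their randomised arm in the intent-to-treat analysis.
3. Use the absence of a medication change only to define a sensitivity analysis, and give one completer definition in both the Interventions and Outcomes sections.
4. Record changes during treatment and report them by arm. The form described under Process measures covers only the period since post-treatment.

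This concerns eligibility wording and analysis sets. It does not touch how medication is managed.

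The cost is a short amendment. The Trial status section reports 68 patients randomised and recruitment still open. Nothing in the article indicates that any of them was removed for this reason; if any was, that patient should be restored to the intent-to-treat set with whatever data exist. The sample size of 50 per arm is unchanged. The downside is that the intent-to-treat estimate will include some effect of medication, which the sensitivity analysis and the report by arm would help readers to judge.
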